## Abstract

**Background:**

Parents play a central role in preventing childhood obesity. There is a need for innovative, scalable, and evidence-based interventions designed to enhance parents’ motivation to support and sustain healthy lifestyle behaviors in their children, which can facilitate obesity prevention.

**Objective:**

(1) Develop an online screening, brief intervention, and referral to treatment (SBIRT) eHealth tool to enhance parents’ concern for, and motivation to, support children’s healthy lifestyle behaviors, (2) refine the SBIRT eHealth tool by assessing end-user acceptability, satisfaction, and usability through focus groups, and (3) determine feasibility and preliminary effectiveness of the refined SBIRT eHealth tool through a randomized controlled trial.

**Methods:**

This is a three-phase, multi-method study that includes SBIRT eHealth tool development (Phase I), refinement (Phase II), and testing (Phase III). 
Phase I: Theoretical underpinnings of the SBIRT tool, entitled the Resource Information Program for Parents on Lifestyle and Education (RIPPLE), will be informed by concepts applied within existing interventions, and content will be based on literature regarding healthy lifestyle behaviors in children. The SBIRT platform will be developed in partnership between our research team and a third-party intervention development company. 
Phase II: Focus groups with parents, as well as health care professionals, researchers, and trainees in pediatrics (n=30), will explore intervention-related perceptions and preferences. Qualitative data from the focus groups will inform refinements to the aesthetics, content, structure, and function of the SBIRT. 
Phase III: Parents (n=200) of children—boys and girls, 5 to 17 years old—will be recruited from a primary care pediatric clinic while they await their children’s clinical appointment. Parents will be randomly assigned to one of five groups—four intervention groups and one control group—as they complete the SBIRT. The randomization function is built into the tool. Parents will complete the eHealth SBIRT using a tablet that will be connected to the Internet. Subsequently, parents will be contacted via email at 1-month follow-up to assess (1) change in concern for, and motivation to, support children’s dietary and physical activity behaviors (primary outcome), and (2) use of online resources and referrals to health services for obesity prevention (secondary outcome).

**Results:**

This research was successfully funded and received ethics approval. Development of the SBIRT started in summer 2012, and we expect all study-related activities to be completed by fall 2016.

**Conclusions:**

The proposed research is timely and applies a novel, technology-based application designed to enhance parents concern for, and motivation to, support children’s healthy lifestyle behaviors and encourage use of online resources and community services for childhood obesity prevention. Overall, this research builds on a foundation of evidence supporting the application of SBIRTs to encourage or “nudge” individuals to make healthy lifestyle choices. Findings from Phase III of this project will directly inform a cluster randomized controlled trial to study the effectiveness of our intervention across multiple primary care-based settings.

**Trial Registration:**

ClinicalTrials.gov NCT02330588; http://clinicaltrials.gov/ct2/show/NCT02330588 (Archived by WebCite at http://www.webcitation.org/6WyUOeRlr).

## Introduction

Childhood obesity is an urgent public health issue. Approximately one-third of Canadian children are overweight or obese [1], a proportion that has doubled over the past 25 years [2]. Pessimistically, the impact of most interventions for managing childhood obesity has been modest to date [3], a point that highlights the need for innovative strategies that are designed to prevent unhealthy weight gain among healthy-weight children (ie, primary prevention) *and* manage excess weight among children with overweight and obesity (ie, secondary prevention). To optimize the effectiveness of such approaches, parents need to play a central role. Specifically, parents set the stage for children’s healthy lifestyle behaviors by fostering a supportive home environment, role-modelling healthy lifestyle habits, and monitoring and reinforcing children’s behaviors [4,5]. Paradoxically, some parents do not perceive their children’s excess weight as a health concern [6], a perception that may be influenced by parents’ inability to accurately recognize obesity in their children [7]. Among parents who have an accurate perception of their child’s weight status (eg, their child meets clinical criteria for obesity *and* parents perceive their child to be obese), only 50 to 60% initiate and sustain healthy lifestyle changes [8]. These results suggest that interventions that attempt to correct parents’ inaccurate perceptions of their children’s weight status *and* enhance their concern for, and motivation to, support children’s healthy lifestyle behaviors may be useful.

Obesity is a common health issue, so interventions to prevent obesity need to be accessible, affordable, and scalable in order to reach a large target audience. The widespread use and availability of the Internet highlights its potential value as a vehicle to deliver obesity prevention interventions [9]—eHealth (electronic health) and mHealth (mobile health) interventions are contemporary terms used to describe health care services and practices that are supported by electronic infrastructure. The benefits of these types of interventions include their ability to offer immediate and tailored feedback, cost-effectiveness, and potential for widespread reach [10]. Web-based interventions may specifically enhance health services by (1) removing social barriers and providing anonymity [11], (2) overcoming limited availability of obesity-related health services [12], and (3) compensating for low confidence and skill levels reported by health care providers [13,14]. Systematic reviews have reinforced such advantages for Web-based interventions for both children [11,15] and parents [16], reporting statistically and clinically meaningful improvements in obesity-related outcomes and lifestyle behaviors.

To date, the majority of online interventions to address obesity-related behaviors have applied time-intensive (eg, online programs up to 52 weeks in length [17]) and resource-intensive (eg, online interventions with additional in-person components [18]) models, suggesting there is value in examining the application of brief and novel online strategies for the prevention of obesity in children [19,20]. One such strategy includes screening, brief intervention, and referral to treatment (SBIRT) approaches, which are time-limited and include an initial screening step followed by the delivery of a short intervention, usually within a 10 to 20 minute period, with options to refer users to treatment and other supportive resources. Fundamental to SBIRTs is the feedback, responsibility, advice, menu options, empathy, and self-efficacy (FRAMES) model [21], which (1) personalizes **f**eedback to communicate unique health outcomes and positive behavior change to the participant, (2) emphasizes personal **r**esponsibility for behavior change, (3) provides **a**dvice on how to initiate and sustain change(s), (4) creates a **m**enu of change options, (5) expresses **e**mpathy, and (6) emphasizes **s**elf-efficacy for change. Historically, SBIRTs have been used to address preventable health concerns (eg, alcoholism, cannabis use) and studies have shown this approach can exert a positive influence on intention to change behaviors as well as behavior change itself [22,23]. SBIRTs are particularly well-suited for obesity prevention in primary care, as providers often have frequent opportunities to interact with families, but limited time and resources to do so. Furthermore, because primary care represents most families’ first point of contact with the health care system [24], the provision of preventative health services, particularly for the primary prevention of chronic diseases, is proactive, efficient, and cost-effective. As well, families tend to access primary care-based health services throughout the life course, so it represents a suitable environment to capture longitudinal data.

With these issues in mind, we hypothesize that an online SBIRT targeting parents will increase their awareness of their children’s weight status and enhance parents’ concern for, and motivation to, support their children’s healthy lifestyle behaviors. The program will have a prevention approach designed to benefit parents with children from across the body weight continuum. Specifically, our SBIRT will encourage parents of children with healthy weights to seek resources to eat healthfully and be physically active to maintain their children’s weight status. It will also guide parents of children with unhealthy weights to access information and health services to improve their children’s weight status and associated health risks. Our three-phase, multi-method study includes the following objectives:

1. Develop an online SBIRT tool designed to raise parents’ awareness of their children’s weight status and lifestyle behaviors.

2. Refine the SBIRT tool by assessing acceptability, satisfaction, and usability using focus groups with pediatric health care professionals, researchers, and parents.

3. Determine the feasibility (pilot-testing) and impact (pragmatic trial) of the intervention through a randomized controlled trial (RCT) design, which will include administering our SBIRT to a sample of parents and collecting data at baseline and 1-month postintervention to assess (1) changes in parents’ concern for, and motivation to, support children’s dietary and physical activity behaviors—primary outcome—and (2) families’ use of resources and health services for the prevention of childhood obesity—secondary outcome.

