### Phase I: Development

Our SBIRT tool, which we have titled the Resource Information Program for Parents on Lifestyle and Education (RIPPLE), will be developed in partnership with Evolution Health (EH), a Web-based intervention development company based in Toronto, Ontario [27]. Content in the SBIRT will be incorporated from current literature on children’s healthy lifestyle behaviors, including dietary, physical activity, and sedentary behavior habits, as seen in Slater et al [28] and a review by Steinbeck [29]. Theoretical underpinnings of the SBIRT will be informed by concepts used in existing interventions, for example, the Norm Activation Model [30]. Consistent with the Health Belief Model [31], the SBIRT will be designed to act as a *cue to action*, in which the intervention will prompt parents to initiate and sustain healthy lifestyle changes for their children. Specifically, the SBIRT will act as a trigger by creating a discrepancy between parents’ perceptions of their children’s dietary and physical activity habits and either *normative* or *injunctive* feedback—parents will receive either *normative* feedback on how their child relates to reference norms drawn from the Canadian pediatric population for eating [32] and physical activity [33], or *injunctive* feedback, which includes national recommendations [34]. By providing parents with two types of feedback, we will determine if injunctive or normative feedback is more salient for parents in the context of supporting their children’s healthy lifestyle behaviors.

Based on SBIRTs previously developed by Evolution Health [35,36], our SBIRT will *screen* children’s weight status, which will include sharing this information with parents, as well as deliver a *brief intervention* to parents related to their children’s lifestyle behaviors, and provide *referrals to treatment* and other supportive resources for parents. Specifically, the guided user interface (GUI) within the online program will include the following steps:

1. Data input. Children’s height (cm) and weight (kg) will be measured by the study-designated research assistant (RA) using a wall-mounted electronic stadiometer and an electronic medical scale. The RA will enter this data into the iPad program and then pass the iPad to the parent.

2. Screening. Parents will receive objective, personalized feedback both numerically, based on their children’s body mass index percentile, and visually, using a healthy weight ruler [37].

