#### Pragmatic Trial

##### Trial Design

A parallel-group, double-blinded randomized controlled trial will be used to assess the effectiveness of the intervention. The trial has been registered publically (ClinicalTrials.gov identification number: NCT02330588) [48] and adheres to CONSORT guidelines [49]. Participants will be recruited and enrolled by an RA and RIPPLE will assign a unique, nonidentifying number to participants. The allocation sequence will be electronically generated within the GUI and to reduce the risk of selection bias, participants (n=200 parents) will be randomly assigned to one of five groups—*Eat It!* (normative), *Eat It!* (injunctive), *Move It!* (normative), *Move It!* (injunctive), or *Heads Up!* (control group). Group assignment will be done using blocked randomization—five arms, block size of five—to ensure equal group sizes—n=40/arm, equal allocation ratio of 1:1—throughout the study. To reduce the risk of performance bias, the RCT will be double-blinded. Specifically, the study-designated RA ([name]) will not be aware of participants’ intervention assignment, unless participants request assistance with the program, thus potentially revealing their assignment. Research personnel will be blinded for the remainder of the research process, including outcome assessment, in order to minimize the risk of detection bias [50]. As well, study participants will not be aware of their assignment to the intervention or control groups. Prior to the intervention, participants will receive information that is sufficient to obtain informed consent, but inadequate so as to decipher between intervention groups. Although contamination is a possibility given the close proximity of participants, given that only one participant can be recruited at a time, enrollment and recruitment will be staggered and the opportunity for participants to discuss the intervention with each other is unlikely.

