Primary health care providers at this site have historically had around 2500 patient encounters per year [51], so our research staff will recruit families on approximately 2 days per week over several months to accumulate our study sample. Given the design of the SBIRT, parents will also need adequate time to complete everything at once (ie, saving and completing the intervention at a later date will not be possible within the SBIRT). With time constraints in mind, families will be approached to participate in the study if we—clinical/administrative staff, research team—believe parents will have sufficient time (ie, 15 to 20 minutes) to complete the intervention and research procedures while waiting for their scheduled clinical appointment. Although it is a potential barrier that some recruited parents may be unable to complete the program while they wait, previous studies have supported the feasibility of brief online interventions under similar conditions, for example, Freeborn et al [52]. Assuming 20 to 30% attrition at 1-month follow-up [53], complete data from approximately 150 parents is expected. Figure 1 represents a flow diagram of expected recruitment and retention. Based on primary care client demography, this sample size will allow us to enroll a diverse group of families that vary by age, ethnicity, family income, and weight status.

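### The tool holds the child's weight category before it assigns the arm, yet allocation is blocked only; stratifying on that category would be a cheap, minor gain in precision and interpretability

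*Protocol article*

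**What the plan says.** The Introduction sets out a single programme for all weights: "The program will have a prevention approach designed to benefit parents with children from across the body weight continuum". It then separates the aims. Parents of healthy-weight children are to be encouraged towards resources that help maintain that weight. Parents of children with unhealthy weights are to be guided towards information and health services.

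Phase I: Development lists the tool's steps in order. In step 1 the research assistant measures height and weight: "The RA will enter this data into the iPad program and then pass the iPad to the parent". Step 2 feeds the BMI percentile back to the parent. Step 3 is random assignment and the assigned module. Step 5 is the questionnaire on concern and motivation.

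Trial Design says that the sequence is generated electronically inside the tool and describes the scheme as follows: "Group assignment will be done using blocked randomization—five arms, block size of five—to ensure equal group sizes". The planned arm size is "n=40/arm, equal allocation ratio of 1:1". No stratification factor is named.

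Data Management and Analysis specifies a hierarchical linear model and neither names nor excludes any covariate. The only use of weight status stated there is descriptive, in looking at who enrols.

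**The concern.** The arms are small, and the trial mixes two groups for whom the programme has different purposes. Blocking equalises arm sizes but does nothing for the mix of weight categories within arms. If that mix differs by chance and weight category is related to the outcome, an individual contrast carries avoidable noise and is harder to explain.

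Study Strengths also says that the results will supply preliminary effect sizes for a later cluster trial. One average over both weight groups is a less informative planning input than the same average with an estimate for each group beside it. The variable that would help is already in the tool before the assignment step.

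**Working it through.** **The plan's own figures.** 200 / 5 = 40 per arm, as stated. For completers, "Assuming 20 to 30% attrition at 1-month follow-up" gives 200 × 0.80 = 160 down to 200 × 0.70 = 140. The stated figure of about 150 is the midpoint, 200 × 0.75, or 30 per arm. The article states no power or effect size, so there is none to reproduce.

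**Inputs.**
- n = 40 per arm at randomisation and 30 per arm at follow-up, from the article.
- p = 1/3 overweight or obese. This is the national figure in the Introduction ("Approximately one-third of Canadian children are overweight or obese"), used as a proxy. The clinic's own value is not given, so 25% to 40% is also shown.
- g = gap in the outcome between weight categories, in within-category SD units. The article gives no value; 0.2, 0.5 and 0.8 are assumed.
- Two-sided α of 0.05, assumed because sidedness is not stated.

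**Step 1: chance imbalance without stratification.** The SD of the difference between two arms in the proportion overweight or obese is √(2p(1−p)/n).
- n = 40: √(2 × 1/3 × 2/3 / 40) = 0.105, a 95% range of about ±21 points.
- n = 30: √(2 × 1/3 × 2/3 / 30) = 0.122, a 95% range of about ±24 points.

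Simulating five binomial arms with n = 40 gives:

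| Event | p = 25% | p = 1/3 | p = 40% |
|---|---|---|---|
| One given intervention arm differs from control by ≥20 points | 5% | 7% | 9% |
| At least one of the four differs from control by ≥20 points | 16% | 22% | 25% |

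With 30 per arm and p = 1/3, the second row becomes 36%.

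**Step 2: what an imbalance does to a contrast.** A 1-SD imbalance shifts the contrast by g × √(2p(1−p)/n). With n = 30 this is 0.02, 0.06 and 0.10 SD for g = 0.2, 0.5 and 0.8.

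**Step 3: validity.** With g = 0.8 and n = 30, the simulated type I error of the unadjusted, unstratified two-arm comparison is 5.1%. The error rate is held.

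**Step 4: gain from a stratum term.** The share of variance explained is R² = p(1−p)g² / (1 + p(1−p)g²). The detectable difference at 80% power is (1.96 + 0.84) × √(2/n) × √(1−R²). With n = 30:

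| g | R² | Detectable difference (SD) | Power for 0.5 SD |
|---|---|---|---|
| unadjusted | – | 0.72 | 49% |
| 0.2 | 0.9% | 0.72 | 49% |
| 0.5 | 5.3% | 0.70 | 51% |
| 0.8 | 12.5% | 0.68 | 54% |

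With n = 40, the detectable difference goes from 0.63 unadjusted to 0.62, 0.61 and 0.59 SD.

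**Step 5: precision within categories.** 30 × 1/3 = 10 overweight or obese completers per arm. The detectable pairwise difference is 2.80 × √(2/10) = 1.25 SD, so estimates within this category can only be descriptive.

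**The case against.** The strongest reply is that leaving allocation unstratified is a legitimate choice in a preliminary trial. Randomisation keeps the comparison valid, chance imbalance is already allowed for in the test's error rate, and enrolling all weights together is the stated intention. All of that stands, and it is why this is an improvement and not an error.

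A reader might infer more, and the article does not support it:

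- **That the model omits weight status.** The analysis section lists no covariates at all. Covariates are commonly left to a full protocol or analysis plan, and neither is shown, so silence is not exclusion. The stratification point does not depend on this, because the allocation scheme itself is described.
- **That weight status is known to drive parental concern.** The Introduction says that some parents do not see excess weight as a health concern, and no link with the outcome is quantified. The outcome is concern and motivation about diet and activity, not about weight.
- **That reassurance about a healthy weight lowers concern and cancels a real effect.** Weight feedback is step 2, before the arms divide, so as listed it is common to all arms. The stated aims are positive for both weight groups. Any figures showing cancellation would have to be invented.
- **That gross imbalance is the norm.** The highest and lowest of the five arms differ by 20 points or more in about 38% of randomisations. That is the most extreme of ten pairs. For one given pair the figure is about 7%.

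**Conclusion.** The point holds as a minor one. Allocation is blocked only, although the weight category is available before the listed assignment step and the programme's aims differ by category. No bias follows, and no false-positive inflation. What is forgone is modest: protection against an intervention arm differing from control by 20 points or more (about 22% of randomisations at 40 per arm, 16% to 25% over the prevalence range), and about 0 to 5 points of power with 30 completers per arm. The weight mix would also be easier to set aside when reading the effect sizes passed to the cluster trial.

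The figures rest on the national prevalence as a proxy for the clinic, on an assumed gap of 0.2 to 0.8 SD, and on a two-sided 5% test. If weight category is unrelated to the outcome, the precision gain is nil and only the interpretability gain remains.

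**What to change.** - Run the tool's existing block-of-five allocation separately within two categories formed from the step 1 measurements: healthy weight, and overweight or obese. Within each category, arm counts can then differ by at most one at randomisation.
- Include that stratum as a term in the hierarchical model.
- Report arm effects by weight category with confidence intervals, labelled as estimates only and not as tests.

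Do not rely on a pre-intervention score as a further covariate. In the listed sequence the questionnaire is step 5, after the module in step 3, so no such score exists.

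The cost is one programming rule, with no new data and no added time for parents. The drawbacks are at most one incomplete block per stratum, so total arm sizes may differ by up to two, and imprecise within-category estimates with about 10 overweight or obese completers per arm. Stratifying balances the arms at randomisation; it cannot guarantee balance among completers after 20% to 30% attrition, which is a further reason to keep the stratum term in the model.
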